#### Modifications

During the training session, we recommend health care providers to regularly discuss the app during treatment. However, due to expected variations in digital literacy and other urgent topics, health care providers are allowed to modify the intensity according to their clinical judgement.

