#### Sample Size Calculation

The sample size calculation is based on a 2-factor repeated-measures analysis of variance with within-factor time (5 levels) and between-factor treatment (2 levels) conditions on the outcome variable PDI. We have set the α to .05, the power (1 – β) to .95, and assumed a moderate treatment effect (*f*=0.2). To account for the expected dependencies of patients within each of the 5 participating treatment locations, we applied the Donner et al [55] formula for the variance inflation factor, assuming an intracorrelation coefficient of 0.2 [56,57]. Furthermore, we corrected the analysis for an expected attrition of 20%, which is based on the average attrition of similar studies that used the PDI [21,58,59]. Based on these calculations, a minimum sample size of 157 participants, equally divided over 5 treatment locations, will be required.

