#### Primary Analysis: Pain Disability

In our primary analysis, we will test the difference in the development of pain disability over time between patients in the enhanced condition and patients in the treatment condition. To account for the assumed dependence of the repeated observations and treatment locations, we will perform a multilevel analysis. In our hierarchical model, time points (level 1) will be nested in patients (level 2) and patients nested in treatment locations (level 3). Our main analysis will include the effects of time, treatment condition, treatment location, and the interaction between time and treatment condition, with a random intercept for patients. In addition, the model will be adjusted for sex, age, pain intensity, and pain duration. In the case of a significant 2-way interaction between time and treatment condition, posthoc contrasts between the treatment conditions at 3, 6, and 12 months will be calculated. We will also perform a subgroup analysis for patients that report a positive treatment effect at t_1_ (ie, a GPE score of 1 or 2).

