#### Analysis of Secondary Outcomes

##### Perceived Usability and App Engagement

Based on the results of the feasibility study and the nature of the behavior regulation strategies, we expect an engagement pattern in frequency, type, and depth of engagement that differs for each behavior change strategy and changes over time. Specifically, for Insight Cards, we believe that patients will actively engage with this component during treatment (ie, creating Insight Cards during use), but shift to more passive engagement (ie, reading the input, but only creating new content at limited occasions) during follow up. For Value-Based Goals, we expect that the formulation of goals and steps will increase during the final part of treatment, together with a growing emphasis within the treatment program on integrating newly learned strategies into daily life routines. After treatment, we anticipate that patients will engage in a reflective (eg, documenting progress) and active (ie, formulating new goals) manner with this strategy. In general, we expect a decreasing trend of the number of logins over time, but an increase in the “depth” of use (ie, the average number of features accessed per login) as well as an increase in the duration of a login. We will calculate descriptive statistics to explore patterns of engagement. Furthermore, to examine the extent to which user engagement and usability are negatively associated with the change of pain disability during follow up, we will perform a multiple regression analysis, with the change score of pain disability (t_4_ – t_1_) as the outcome variable and engagement and usability measures as predictors. We will adjust for age, sex, pain intensity, and baseline PDI.

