### Participant Timeline

Patient eligibility screening, informed consent, and treatment allocation procedures, as well as the baseline assessment, will be completed prior to the start of the treatment program. Patients in the enhanced treatment condition will receive instruction on how to download and use the app, and both strategies will be explained by a member of the treatment staff. To match the existing treatment content and procedures, the moment that the app will be introduced to patients can vary between locations. During the treatment phase, the app is considered a supplement to the main treatment activities and patients are free to decide how and when to use the app. Health care providers will be instructed to encourage and facilitate using the strategies when they expect it will reinforce the treatment process. However, both strategies can largely be used independently of any treatment activity and are expected to minimally affect direct treatment time. A member of the research team will be available to the treatment staff throughout the experimental phase for additional questions, support, and discussions regarding optimal use. Following treatment, there will be no additional monitoring in the enhanced treatment condition. Patients will continue to be able to use the app at their discretion. Posttreatment data will be obtained directly posttreatment (t1), and at 3 months (t2), 6 months (t3), and 12 months (t4) posttreatment.

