This study includes several challenges and compromises that can potentially bias the outcomes. First, including patients with both treatment conditions within one center increases the risk of contamination. Second, health care providers have a large influence on participant engagement. Our feasibility study indicated that health care provider involvement varied greatly between patients, and that patients with limited health care provider feedback did not always use the intervention as intended (see personal communication, [name]; manuscript under review). By scheduling regular contact moments to discuss progress, we aim to minimize the impact of this potential threat. Third, the limited project duration and funding resulted in a maximum follow-up period of 12 months. Although this first year may be crucial for integrating the newly learned management strategies into a daily life routine, the effect of the AGRIPPA app on late-onset occurrences of relapse will not be monitored in this study. Limited funding also prevented the development of an active (mHealth) control condition. Although opting for a treatment-as-usual condition as a comparator is a widely used method, this does not control for the potential placebo effect of receiving an mHealth app. Fourth, to minimize the impact for patients to participate in this study, we have selected a limited number of outcome measures and measurement time points in addition to routine assessments. This may result in an increased recall bias or limited insight in potential factors that could explain a possible effect of the app. Finally, patients will require sufficient digital literacy skills to effectively use the app, which may lead to self-selection during the recruitment phase. The selection bias may threaten generalization.

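### The engagement and usability regression leaves out treatment location, so site differences can be read as an association with app use

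*Protocol article*

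**What the plan says.** The section Perceived Usability and App Engagement sets out a multiple regression "with the change score of pain disability (t_4_ – t_1_) as the outcome variable and engagement and usability measures as predictors", followed by "We will adjust for age, sex, pain intensity, and baseline PDI". Table 1 names the same method, multiple linear regression. Location is neither a covariate nor a level. The hypothesis, under Study Objectives, concerns the enhanced treatment arm only and is directional.

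The primary model is built differently: "Our main analysis will include the effects of time, treatment condition, treatment location, and the interaction between time and treatment condition". The stated reason is "To account for the assumed dependence of the repeated observations and treatment locations, we will perform a multilevel analysis". The Sample Size Calculation inflates for patients within locations, "assuming an intracorrelation coefficient of 0.2".

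On how app use may depend on the site, Participant Timeline says that "the moment that the app will be introduced to patients can vary between locations". Component 3: Information and Education lets each centre add its own material to the app. Adherence to the Intervention Protocol has each team settle when the app is introduced and by whom. Standard Treatment and Strengths and Limitations both say that programmes differ in content between centres.

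**The concern.** Location can act on both sides of this regression. It can affect engagement, through when and how the app is introduced and what the centre puts in it. It can affect the course of disability after treatment, through the programme and team. None of the four listed covariates captures programme or team, and randomisation gives no protection because engagement is compared among app users only.

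A centre with a stronger programme could show both more app use and better maintenance, and so produce an association even if use makes no difference within a centre. Separately, an ordinary regression treats patients of one centre as independent. If engagement and PDI change both cluster by centre, the standard error is too small even without a directional bias.

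At stake is the reading of Hypothesis 3. The Discussion (Study Goals) says the analysis will test the impact of engagement and usability on disability, so a site pattern could be reported as support for the app.

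**Working it through.** **1. The plan's own figure.** The article gives no calculation for the engagement regression; its only computed figure is the total of 157. Inputs from Sample Size Calculation: f = 0.2, 5 time points, 2 groups, α = 0.05, power 0.95, ICC 0.2, 5 locations, attrition 20%. Assumed, because not stated: correlation of 0.5 between repeated measures. The within-between interaction test, with noncentrality f² × N × 5 / (1 − 0.5), needs N = 48. The variance inflation is 1 + (48/5 − 1) × 0.2 = 2.72. Then 48 × 2.72 = 130.56, and 130.56 × 1.2 = 156.67, rounded up to 157. On these inputs the ICC of 0.2 by location is a working part of the plan, for the outcome PDI.

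**2. Patients in the engagement regression.** Planned recruitment is 158, allocated 1:1, so about 79 have the app. The outcome needs 12-month data: 79 × 0.8 = 63.2, about 63. Over the 6 locations in Study Setting that is 63/6 = 10.5 per location.

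**3. Effect of clustering alone.** The usual approximate variance factor for a regression slope is 1 + (m − 1) × ICC(engagement) × ICC(outcome). With m = 10.5, an assumed engagement ICC of 0.2 and an outcome ICC of 0.2 borrowed from PDI: 1 + 9.5 × 0.04 = 1.38. The standard error ratio is √1.38 = 1.17, and 2 × P(Z > 1.96/1.17) is about 9.5%.

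**4. Simulation of the stated model.** Setting: 63 app users, 6 locations, outcome ICC 0.2, true within-location slope zero, four covariates, 3000 runs per case. The model as written was compared with the same model plus location indicators. Assumed: the engagement ICC, and the location-level correlation r between engagement and PDI change (negative means that sites with more use have more favourable change). Two-sided rejection rates at nominal 5% for the model as written, with the mean standardised slope in brackets:

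| Engagement ICC | r = 0 | r = −0.5 | r = −0.8 |
|---|---|---|---|
| 0 | 4.7% (0.00) | – | – |
| 0.1 | 7.0% (0.00) | 9.4% (−0.06) | 12.8% (−0.09) |
| 0.2 | 8.7% (0.00) | 14.0% (−0.08) | 20.4% (−0.13) |
| 0.3 | 8.6% (0.00) | 18.5% (−0.11) | 27.6% (−0.16) |

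With location indicators, the mean slope is about zero and the rejection rate lies between 4.6% and 6.0% in all the cases run with outcome ICC 0.2.

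**5. Sensitivity.** With 5 locations, engagement ICC 0.1 to 0.3 gives 7.8% to 11.3% at r = 0 and up to 26.9% at r = −0.8. With a smaller outcome ICC of 0.05 or 0.10 and engagement ICC 0.2, the rates run from 5.2% (ICC 0.05, r = 0) to 13.5% (ICC 0.10, r = −0.8).

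**The case against.** **The ICC belongs to another outcome.** A reader might infer that the plan's own ICC of 0.2 contradicts independent errors here. It does not: that figure is for PDI, and this outcome is the change t4 − t1. A constant location shift in PDI cancels in the change score, and the primary model has location as a main effect without a location-by-time term. That locations differ in change is plausible because programmes differ, but it is an assumption. This objection stands, and it is why the size is only illustrative.

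**A larger error rate is tempting.** Using all 79 app patients (13.2 per location) and the full factor 1 + 12.2 × 0.2 = 3.4 gives a standard error ratio of 1.85 and a rejection rate of about 29%. That requires engagement to be identical for every patient at a site, and it ignores the 20% attrition. With an engagement ICC of 0.2 the factor is 1 + 12.2 × 0.04 = 1.49, or about 11%. Nothing in the article says engagement varies mainly between sites, and Participant Timeline leaves use to the patient. The 29% is not supported.

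**Provider behaviour is not stated by location.** A reader might take "health care providers are allowed to modify the intensity according to their clinical judgement" and "health care providers have a large influence on participant engagement" as evidence of site differences. The passages around them describe variation by clinical judgement and between patients. Only the timing of introduction and the added content are stated by location; differing encouragement is an inference from team-level arrangements.

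**The analysis is modest in rank.** Strengths and Limitations calls it exploratory, and the hypothesis speaks of association. That limits the weight of the point but does not answer it, because the hypothesis is pre-stated and the Discussion speaks of impact.

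**Adjusting has a price.** Fixed location effects discard between-site differences in engagement. This is true, but that is the variation that cannot be separated from programme and team.

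**Conclusion.** The point holds as a weakness of a secondary analysis. The article fixes an explicit covariate list without location, while its primary model includes location and it describes differences between sites in app introduction, app content and programme. If locations differ in both engagement and PDI change, site differences can be read as an association with app use, and the standard errors ignore clustering.

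How large this is cannot be settled from the documents. It depends on the ICC of PDI change, the ICC of engagement and the site-level correlation between them, none of which is given. On the main assumptions above (6 locations, outcome ICC 0.2, engagement ICC 0.1 to 0.3), the false-positive rate is about 7% to 9% with no site-level correlation and up to about 28% with a strong one. The spurious standardised slope ranges from 0 to −0.16. If engagement does not differ by location, the rate stays near 5% and there is no bias.

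It would go too far to say that site differences will be read as an effect of the app: a directional bias needs the site-level correlation. The randomised primary comparison is not affected.

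**What to change.** Add treatment location as a fixed factor to the engagement and usability regression, consistent with the primary model. With 5 or 6 locations, fixed effects are preferable to a random effect. Report the engagement descriptives by location alongside, and describe the result as a within-location association. Patient-level motivation can still confound it, so adjustment for location does not turn it into an effect of use.

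The cost is one sentence of analysis text and no new data. Six locations take 5 degrees of freedom. If all seven usage measures, the usability score and the four covariates enter one model, residual degrees of freedom fall from 63 − 13 = 50 (counting the intercept) to 45. Between-location variation in engagement no longer contributes to the estimate.

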##### Cost Effectiveness

To investigate the efficiency of the intervention, we will perform a cost-effectiveness analysis at 3 and 6 months posttreatment according to the intention-to-treat principle. We hypothesize that patients in the enhanced treatment condition will have more quality-adjusted life years (QALYs) relative to the health care expenses compared to the regular treatment condition within the 6-month study period. Expected health gain will be expressed in QALYs and calculated using the procedure of Brazier and colleagues [60] to estimate the 6-dimensional health state form (SF-6D) using the SF-12 assessment at 3 and 6 months posttreatment [39,61]. Intervention costs will be determined by the standardized cost prices for rehabilitation treatment [62]. Other health expenses will be obtained using the iMTQ at 3 and 6 months posttreatment. This questionnaire includes visits to health care providers, prescribed and over-the-counter medication, and alternative health care. We will also calculate the productivity loss due to pain-related absence from work, adopting the gross human capital approach [63]. Productivity loss will be obtained with two questions of the iPCQ at 3 and 6 months posttreatment. Total costs are calculated using the Dutch manual for cost analysis in health care research [62,64]. Following the procedure of Den Hollander and colleagues [65], a standardized cost price will be used for each hour of productivity loss. Total costs and total health gains for each condition will be used to calculate the incremental cost-effectiveness ratio (ICER). Furthermore, we will construct cost-effectiveness acceptability curves based on mean costs and using incremental costs and incremental effects, employing nonparametric bootstrapping with 5000 replications. This will result in a scatter plot over four quadrants, where each quadrant indicates a different implication for economic evaluation (ie, a combination of positive or negative costs and effects) [66].

According to the National Institute for Health Care and Excellence guidelines, all intervention costs in cost-effectiveness analyses should relate to health care or social services funding [67,68]. This excludes the development costs of the AGRIPPA app because this project has been funded with research grants. However, to account for future development and maintenance costs, we will perform a sensitivity analysis and explore various cost scenarios. We will calculate multiple ICERs, each with a different cost input value that corresponds to a possible future pricing scenario (eg, subscription, pay to download).

##### Missing Data

Following recommendations of Twisk and colleagues [69], we will perform the multilevel analysis on incomplete data, rather than using multiple imputation procedures. However, we will use the R MICE package to search for patterns of missing data across the included variables and to perform *t* tests to explore the relationships between the amount of missingness of each variable and all other variables [70].

### Participant Timeline

Patient eligibility screening, informed consent, and treatment allocation procedures, as well as the baseline assessment, will be completed prior to the start of the treatment program. Patients in the enhanced treatment condition will receive instruction on how to download and use the app, and both strategies will be explained by a member of the treatment staff. To match the existing treatment content and procedures, the moment that the app will be introduced to patients can vary between locations. During the treatment phase, the app is considered a supplement to the main treatment activities and patients are free to decide how and when to use the app. Health care providers will be instructed to encourage and facilitate using the strategies when they expect it will reinforce the treatment process. However, both strategies can largely be used independently of any treatment activity and are expected to minimally affect direct treatment time. A member of the research team will be available to the treatment staff throughout the experimental phase for additional questions, support, and discussions regarding optimal use. Following treatment, there will be no additional monitoring in the enhanced treatment condition. Patients will continue to be able to use the app at their discretion. Posttreatment data will be obtained directly posttreatment (t1), and at 3 months (t2), 6 months (t3), and 12 months (t4) posttreatment.

## Results

The trial has been registered in the Netherlands Trial Register under the identifier NL8076. The study is ongoing. The patient inclusion period started in October 2019 and is expected to end in November 2020. As of March 20, 2020, we have recruited 88 patients. Results are expected to be released in the final quarter of 2021. In the last meeting of 2020, the steering committee will initiate the formation of writing teams that will be responsible for the final trial report.

## Discussion

### Study Goals

This study will evaluate the AGRIPPA app in the context of interdisciplinary multimodal pain treatment programs. Specifically, we will investigate the effect of app use on long-term pain disability and efficiency by means of a cost-effectiveness analysis. To discover how patients interact with the app, we will also explore usability and engagement and test the impact of these variables on pain disability. Together, these analyses will help to demonstrate to what extent the AGRIPPA app contributes to preventing relapse in pain-related disability.

In contrast to prevailing intervention development guidelines, the AGRIPPA development project adopted a co-design approach and started with collecting qualitative data from end users (eg, patients and health care providers) rather than with formulating a theoretical framework. Although co-design is increasingly acknowledged in the health care domain as a method to integrate stakeholder input into the intervention design, more robust evaluations of co-design–based interventions are required to determine its additional value to existing development practices [71,72]. A similar point can be made for the evaluation of mHealth apps. A recent systematic review revealed that health care apps to promote self-management in chronic conditions have seldom been evaluated by randomized controlled trials over a prolonged study period [27]. This study will help understand if an mHealth app that has been developed by co-design methods not only contributes to an acceptable and user-friendly intervention but also leads to maintenance of treatment gains for patients with chronic pain.

### Strengths and Limitations

Because IMPT programs often substantially vary in dose and content, the inclusion of multiple treatment centers will positively influence generalization. Furthermore, this study builds on a feasibility study where evaluations related to form, content, and integration within treatment programs have been incorporated into the current app and study procedures.

The exploratory analysis of engagement variables in this study is expected to provide preliminary insight into patient adherence to the behavior regulation strategies within the app. According to Sieverink and colleagues [73], insight into adherence to mHealth apps can be acquired by combining usage behavior data with a description of intended use and a well-substantiated justification for this intended use. Although this may be difficult to quantify as the intended usage of the app depends on fluctuations of patients’ functional status in the posttreatment phase, the comparison of system usage data with our expectations regarding the use of the strategies will at least provide an indication of adherence to the app. Possible follow-up studies that include qualitative evaluations of patient input may lead to a more sustained insight into adherence.

This study includes several challenges and compromises that can potentially bias the outcomes. First, including patients with both treatment conditions within one center increases the risk of contamination. Second, health care providers have a large influence on participant engagement. Our feasibility study indicated that health care provider involvement varied greatly between patients, and that patients with limited health care provider feedback did not always use the intervention as intended (see personal communication, [name]; manuscript under review). By scheduling regular contact moments to discuss progress, we aim to minimize the impact of this potential threat. Third, the limited project duration and funding resulted in a maximum follow-up period of 12 months. Although this first year may be crucial for integrating the newly learned management strategies into a daily life routine, the effect of the AGRIPPA app on late-onset occurrences of relapse will not be monitored in this study. Limited funding also prevented the development of an active (mHealth) control condition. Although opting for a treatment-as-usual condition as a comparator is a widely used method, this does not control for the potential placebo effect of receiving an mHealth app. Fourth, to minimize the impact for patients to participate in this study, we have selected a limited number of outcome measures and measurement time points in addition to routine assessments. This may result in an increased recall bias or limited insight in potential factors that could explain a possible effect of the app. Finally, patients will require sufficient digital literacy skills to effectively use the app, which may lead to self-selection during the recruitment phase. The selection bias may threaten generalization.

